## Abstract

**Background:**

Patients with non-acute spinal cord injury that carry indwelling urinary catheters have an increased risk of urinary tract infection (UTIs). Antiseptic Silver Alloy-Coated Silicone Urinary Catheters seems to be a promising intervention to reduce UTIs; however, actual evidence cannot be extrapolated to spinal cord injured patients. The aim of this trial is to make a comparison between the use of antiseptic silver alloy-coated silicone urinary catheters and the use of standard urinary catheters in spinal cord injured patients to prevent UTIs.

**Discussion:**

The aim of this study is to assess whether silver alloy-coated silicone urinary catheters improve ITUs in spinal cord injured patients. ESCALE is intended to be the first study to evaluate the efficacy of the silver alloy-coated catheters in spinal cord injured patients.

**Trial registration:**

NCT01803919

## Background

Most patients with spinal cord injuries (SCI) suffer from some type of neurogenic lower urinary tract dysfunction which requires the use of different strategies for voiding, including urinary catheters. Almost all patients with indwelling urinary catheters develop bacteriuria and in consequence urinary tract infections (UTI) occur frequently. Frequent UTI are bothersome for the patients, implies frequent antibiotic use and increase of resistant strains, may cause septicemia and are therefore related to a decreased health-related quality of life [1-3].

Several trials have evaluated the effectiveness of different types of indwelling urinary catheters to prevent urinary infections in hospitalized adults requiring short-term catheterization. A systematic review of randomized controlled trials revealed that silver-alloy but not silver-oxide coated catheters, were associated with a significant reduction in bacteriuria in comparison to standard catheters [4]. Another recent systematic review aimed to determine which type of indwelling urinary catheter is best to use for long-term bladder drainage in adults found that all trials were small and with methodological weaknesses. The evidence from this systematic review was not sufficient as a reliable basis for practical conclusions [5].

A large randomized clinical trial assessing three different catheters (silver-alloy-coated, nitrofural-impregnated and a PTFE-coated catheters) in hospitalized adults with acute pathologies requiring short urinary catheterization has been recently published. No clinically relevant difference was noted between the three groups [6].

Few randomized clinical trial have evaluated the effectiveness of different catheters in SCI population, most of them assessing the use of intermittent catheterization, but none using antiseptic-impregnated catheters [7-11].

We propose a clinical trial in SCI patients needing an indwelling urethral catheter to assess the effectiveness of urinary catheters with antiseptic, silver-alloy coating. The study hypothesis is that the use of these urinary catheters reduces the risk of UTI compared to the use of conventional urinary catheters.

## Methods/Design

### Study design

This study is an open, randomized, multicentre, and parallel clinical trial. Local ethics approvals have been obtained from all centres participating in this study

### Participants

Seven-hundred and forty-two participants in this study are being recruited from rehabilitation or spinal units at specialized hospitals and outpatient centres across Spain (Table 1 and ESCALE group in Additional file 1). The inclusion period is from November 2012 to December 2014.

**Table 1 T1:** Participating centers

**Coordinating centre:**	
**Iberoamerican Cochrane Centre. Institute of Biomedical Research (IIB Sant Pau), Barcelona**	
Recruiters centers:	
1	Complexo Hospitalario Universitario A Coruña
2	Hospital Universitario Central de Asturias
3	Complejo Hospitalario Universitario Insular – Materno Infantil de Canarias
4	Hospital Universitario Cruces, Barakaldo.
5	Hospital Universitario Miguel Servet, Zaragoza
6	Hospital Universitario La Paz, Madrid
7	Hospital Nacional de Parapléjicos de Toledo
8	Hospital Universitario Virgen del Rocío, Sevilla
9	Hospital de Neurorrehabilitación - Instituto Guttmann, Badalona
10	Hospital Universitario Puerta del Mar, Cadiz

This yields the inclusion of patients with first-ever urethral catheterization and also patients with indwelling urethral catheterization as a method of voiding.

The criteria for inclusion in this study are:

1. Male or female patients with traumatic or medical spinal cord injury.

2. Age of 18 years or above.

3. Patients who need an indwelling urinary catheter as a method of bladder drainage for at least 7 days.

4. Patients who are willing to participate in the study and give their written informed consent (If a patient is unable to give written consent because of physical or mental disability, an affirmation of consent will be taken in his presence from his relative or legal guardian).

The following participants will not be included in the study:

1. Patients who can benefit from other method of bladder drainage such as intermittent catheterization, suprapubic drainage or reflex voiding; as well as those using an external collector.

2. Patients with urinary tract infection at the moment of inclusion.

3. Current antibiotic use or use within 7 days prior to inclusion.

4. Outpatients with sporadic medical examinations (less than one per month).

5. Known allergy to latex, silver salts or hydrogels.

6. Patients with surgical interventions in the urinary tract that may interfere, at the investigator criteria, with the study results.

7. Pregnant or breastfeeding woman.

Subjects eligible for the study are contacted through medical staff and are provided with information about the study (verbal and written information). Consent is then obtained for participation in the study.

### Procedures

#### Interventions

Participants are randomly allocated to intervention or control arms.

The intervention arm receives urinary catheters with antiseptic silver alloy coating (BIP Foley catheter – Silicone, Bactiguard® Infection Protection). Bactiguard® Infection Protection coating consists of noble metals such as gold, palladium and silver and its mechanism of action is to avoid the adhesion of bacteria to the inner catheter surface. All are made of full silicone.

The control arm receive standard urinary catheters commonly used in each hospital, most of them made of silicone or silicone-latex.

Trained health staff performs urethral catheterization procedure and select the most adequate catheter size. To ensure aseptic conditions they are asked to strictly follow the current protocol in their respective centres. Indwelling urethral catheters are periodically replaced about 30 days of use; to not interfere with current clinical practice, the policy of each centre (or the investigator criteria) for catheter replacement and removal is considered valid for this study.

##### Blinding

This study is not blinded and the patient and health staff will know whether the patient is allocated to intervention or control arms. Differences in the shape and color of urinary catheters made study blinding too complex. To prevent bias the primary outcome will be evaluated by a data adjudication committee blinded to the intervention.

##### Randomization

The random sequence for the two comparison groups is computer generated ensuring equal allocation ratio. Blocked stratification for study centre is used to ensure that the two groups do not differ between centres. On-line central randomization ensures that intervention allocation is properly concealed.

Due to the characteristics of the included patients, it would be possible that they still require the use of an indwelling urinary catheter after their participation in the study. The study allows the participants to be randomized more than once if all the inclusion and exclusion criteria are still valid. Between first and subsequent participation in the study, patients should use standard catheters.

##### Data collection

All data is collected through an on-line electronic data capture system (http://ensayoescale.com). Secure access to this on-line platform is restricted to each centre investigator and designed collaborators and ensured by individual passwords.

The study on-line platform collects from each participant the inclusion and exclusion criteria, baseline clinical and demographic data, the allocated intervention (size, reference number, and whether the aseptic conditions are observed), any sign and symptom which may be suggestive of acute UTI, results from urine and/or blood analysis (if performed), antimicrobial susceptibility test (if performed), any treatment given, adverse events as well as the data and reason for urinary catheter replacement or removal.

See Figure 1 for the study flow diagram.

**Figure 1 F1:**
[figure not shown]
Study flow diagram.

#### Measures

##### Socio-demographic and baseline clinical data

The following data are registered: date of birth, gender, level of spinal cord injury, traumatic or medical causes of spinal cord injury, ASIA scale [12], time with indwelling urethral catheter or first-ever urethral catheterization, presence of diabetes mellitus and medical treatments history (including treatments that may increase risk of infection).

##### Primary outcome

The primary outcome is the development of a UTI related to urinary catheterization.

The patient must have at least one sign or symptom suggestive of UTI (see Table 2) with no other recognized cause and a positive urine culture with no more than 2 species of microorganisms. The study does not establish a specific threshold of uropathogen colony count criteria for the diagnosis of UTI and use each centre criteria.

**Table 2 T2:** Signs and symptoms suggestive of urinary tract infection

Increased spasticity	Costovertebral pain or tenderness
Fever (body temperature > 38°C)	Foul-smelling urine
Chills	Change in urine colour
Profuse sweating	Change in voiding patterns
Dysuria	Autonomic dysreflexia
Suprapubic pain or tenderness	Any other sign or symptom that to the investigator criteria may be suggestive of UTI
Abdominal pain or tenderness	

An UTI is considered associated with the use of study catheter if the specimen collection is performed at any time from catheterization procedure and 30^th^ day, catheter removal or catheter replacement (whichever occurs first).

It was considered that knowing if one type of urinary catheter or another may reduce symptomatic UTI is critical for clinical decisions. Many other studies considered asymptomatic bacteriuria (ASB) as primary outcome but ASB is very common in SCI patients, especially in those using indwelling catheters, and it appears to have no long-term squeals [13].

##### Secondary outcomes

Asymptomatic UTI, bacteremic UTI, and adverse events related to catheterization procedure are considered secondary outcomes.

Patients with an asymptomatic UTI are those with no signs or symptoms but with a positive urine culture with no more than 2 species of microorganisms in an specimen collected at any time from catheterization procedure and 30^th^ day, catheter removal or catheter replacement (whichever occurs first).

Patients with bacteremic UTI are those fulfilling the primary outcome and with a positive blood culture with at least 1 matching uropathogen microorganism to the urine culture.

The study measures the direct costs attributable to the use of intervention or control urinary catheters and their complications.

Any untoward medical occurrence in a patient using catheters with antiseptic silver alloy coating or standard catheters under study are also recollected.

### Statistical analysis

Primary efficacy analysis will be performed on the intent to treat population set, including those participants correctly randomized and willing to participate in the study. Per protocol analysis will also be performed including those participants correctly randomized, willing to participate and with no major protocol violations. A further exploration of the sensitivity will be performed with these two sets of population to check they lead to the same conclusions. Primary and secondary outcome analyses including dichotomous data will be analyzed using Chi-squared test (or Fisher’s exact test if analysis sample size is small). Socio-demographic and baseline clinical data will be described providing mean and standard deviation (or median and range) and compared using ANOVA test (or Kruskall-Wallis test) depending whether the data fulfil the application requirements.

In addition a regression analysis depending on gender, lesion level, re-inclusion and indwelling urethral catheterization carriers, first-ever catheter or another significant or clinical relevant outcome will be considered. No interim analysis is planned.

The level of significance will be the usual 5% (alpha = 0.05), two-sided. All the analysis will be performed with SPSS (V19.0).

Power calculation: The sample size was calculated on the assumption that 24% of patients will suffer from an UTI related to urinary catheterization, and a relative reduction of 35% with the use of catheters with antiseptic silver alloy coating, which is considered clinically relevant. A total sample size of 742, 371 in each group (allowing for 5% attrition) have a minimum of 80% power to detect these differences between intervention groups.

There is very limited information on the overall incidence of UTI in SCI patients using indwelling catheters, most coming from observational studies that included patients using different voiding methods, with a variety of risk factors, using heterogeneous definitions of UTI. In addition follow-up periods and incidence measures used varied broadly. We thus considered, conservatively, that almost one quarter of participants will suffer from an UTI [14,15].

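### Randomisation is stratified by centre but the primary chi-squared test is not: the test is valid and keeps about 80% power, yet it forgoes some power that a centre-stratified test would give

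*Protocol article*

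**What the plan says.** **Design.** Under Randomization, the Protocol article says that "Blocked stratification for study centre is used to ensure that the two groups do not differ between centres", with a sequence that is "computer generated ensuring equal allocation ratio". Table 1 (under Participants) lists 10 recruiting centres.

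**What is left to the centres.**
- The comparator (Interventions): "The control arm receive standard urinary catheters commonly used in each hospital, most of them made of silicone or silicone-latex".
- Catheter replacement and removal (Interventions): each centre's policy, or the investigator's judgement, is accepted. Under Primary outcome, a UTI counts only up to day 30, removal or replacement, so this policy also sets how long a patient is at risk.
- The culture criterion (Primary outcome): "The study does not establish a specific threshold of uropathogen colony count criteria for the diagnosis of UTI and use each centre criteria".

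**Analysis.** Under Statistical analysis, "Primary and secondary outcome analyses including dichotomous data will be analyzed using Chi-squared test", or Fisher's exact test if the sample is small. A regression is mentioned as an addition. It names gender, lesion level, re-inclusion, and existing carrier versus first-ever catheter, and then adds that "another significant or clinical relevant outcome will be considered". Centre is not named there, and nothing else in the article brings centre into an analysis.

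**The concern.** Blocking within centre balances the arms inside each centre, so differences between centres largely drop out of the treatment comparison. An unstratified chi-squared test still counts those differences as random error. If centre rates differ, its standard error is too large: the true type I error falls below 5%, and the test is less powerful than one that uses the strata.

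Three practices that bear on the outcome are set locally (comparator, length of the at-risk window, laboratory criterion). That is good reason to expect centre UTI rates to differ here. The article names the primary test itself, so this is a choice it has made and not a detail left to an unseen analysis plan.

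What is at stake is efficiency. The sample size gives about 80% power with little reserve, and a stratified test recovers some power at no cost in patients.

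**Working it through.** **Inputs from the Protocol article (Statistical analysis, Randomization, Table 1).** Control rate 24%; relative reduction 35%, so 0.24 × 0.65 = 0.156 in the silver arm, a difference of 0.084; two-sided alpha 0.05; power 80%; attrition 5%; 742 in total, 371 per arm; 1:1 allocation; 10 centres.

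**Input not in the documents.** The between-centre spread of UTI rates. It is assumed below as an SD of the centre log-odds, over a range.

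**Step 1. Reproduce the sample size.** For two proportions with pooled variance and no continuity correction,

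n = [1.960 × √(2 p̄(1 − p̄)) + 0.842 × √(p₁(1 − p₁) + p₂(1 − p₂))]² / (p₁ − p₂)².

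With p̄ = 0.198: n = [1.960 × √0.3176 + 0.842 × √0.3141]² / 0.084² = 1.576² / 0.007056, which gives 353 per arm. For attrition, 353 × 1.05 = 371 and 353 / 0.95 = 372. The stated 371 per arm reproduces. Power is 80.1% with 353 evaluable per arm, and 82.0% if all 371 are evaluable. The figure was computed for an unstratified test.

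**Step 2. Direction of the effect.** With 1:1 allocation within centres and no treatment effect, the unstratified test uses the variance p̄(1 − p̄). The variance that the design actually leaves is the average of p_k(1 − p_k) over centres k, which equals p̄(1 − p̄) − Var(p_k). The test therefore overstates the variance by Var(p_k), and is exact only if centres do not differ.

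**Step 3. Size of the effect.** Simulation of 100,000 trials per scenario: 10 equal centres, 350 evaluable per arm (35 per arm per centre), a common odds ratio within centres, and overall rates held at 24% and 15.6%. The Cochran-Mantel-Haenszel (CMH) statistic is z = Σ(x_k − m_k/2) / √ΣV_k. Here V_k = n_k² m_k (T_k − m_k) / [T_k² (T_k − 1)], x_k is the number of control events, m_k all events, n_k the patients per arm and T_k = 2n_k.

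| SD of centre log-odds | Centre control rates | Type I error, chi-squared | Type I error, CMH | Power, chi-squared | Power, CMH | Power forgone (points) |
|---|---|---|---|---|---|---|
| 0 | 24% | 5.0% | 5.0% | 79.9% | 80.0% | about 0 |
| 0.25 | 17–33% | 4.8% | 5.0% | 79.8% | 80.1% | 0.3 |
| 0.5 | 11–42% | 4.6% | 5.1% | 80.5% | 81.5% | 1.0 |
| 0.75 | 7–51% | 4.0% | 5.0% | 80.8% | 83.0% | 2.2 |
| 1.0 | 4–59% | 3.5% | 5.2% | 81.4% | 85.1% | 3.7 |
| 1.5 | 1–73% | 2.2% | 4.9% | 83.5% | 89.7% | 6.3 |

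The simulation error of a power near 80% is √(0.8 × 0.2 / 100,000) = 0.13 points.

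**Step 4. Sensitivity.** With unequal centres (25% of patients in the largest, 3% in the smallest; 354 per arm), CMH gains 0.3, 0.8, 1.6 and 3.7 points at SD 0.25, 0.5, 0.75 and 1.0. Another run with unequal centres and 706 evaluable patients gave 80.6% against 81.5% at SD 0.5, and 81.1% against 83.9% at SD 1.0. A further run gave 80.9% against 82.9% at SD 0.75, and 81.3% against 84.6% at SD 1.0. All agree.

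No run models patients who are randomised more than once.

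**The case against.** **No shortfall against the plan.** The article promises at least 80% power. The planned test delivers 79.8% to 83.5% across the table, and 742 was sized for exactly this test. This stands. A reader might infer that the trial is underpowered or the sample size wrong. The documents do not support that: the loss exists only relative to a stratified test.

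**The error is on the safe side.** Type I error stays at or below 5% apart from simulation noise, and the primary comparison is not biased. This also stands.

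**The spread is unknown.** A reader might infer that centre rates must differ because practice is set locally. The documents show local discretion, not its effect on UTI rates. Most control catheters are described as silicone or silicone-latex, replacement is at about 30 days, and one blinded committee adjudicates the primary outcome, which may narrow differences in classification. So a difference is to be expected, but its size is not established.

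**The regression clause is secondary.** Read literally, "another significant or clinical relevant outcome will be considered" lets post-randomisation outcomes serve as covariates. That reading goes too far. The regression is additional and only to be considered, the named factors are baseline characteristics, and the last noun is probably loose wording for a variable. What remains is that admitting covariates because they are significant is data-driven, in an analysis that cannot change the primary result.

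None of this gives a reason to leave the stratification factor out. With no centre variation the stratified test costs nothing (79.9% against 80.0%).

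**Conclusion.** The point holds as a recommended improvement, not as an error that endangers the trial. The article stratifies randomisation by centre and then fixes a primary test that ignores centre. That test is valid, mildly conservative and still has about the stated 80% power. Relative to a centre-stratified test it forgoes about 0 to 2 points of power for no to moderate centre variation (SD up to 0.75), and about 3 to 4 points at SD 1.0. More would be lost only with very wide spreads, for which the documents give no basis.

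The figures rest on the assumed spread, a common odds ratio within centres, overall rates of 24% and 15.6%, and independent records. The article allows patients to be randomised more than once, so the last assumption is not met in full. That is a separate issue, which CMH does not solve either.

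**What to change.** 1. Make the primary test a CMH test stratified by centre, or a logistic model with centre as a factor, with a prespecified rule for pooling very small centres.
2. Report the Mantel-Haenszel risk difference with its 95% confidence interval: Σw_k d_k / Σw_k, with w_k = n₁k n₂k / T_k and d_k the difference in centre k. It can be set directly against the target of 84 fewer UTIs per 1000 given in the Discussion.
3. As a minor point, add centre to the additional regression, limit it to the named baseline variables, and delete the clause that admits further factors by significance.
4. Deal with repeat randomisation of the same patient separately, and keep centre in whatever method is chosen for it.

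The cost is wording only. Centre is already recorded for randomisation, and neither extra data nor a change to the sample size of 742 is needed.

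### The primary chi-squared test is valid and correctly sized, but leaves baseline factors already collected to an optional extra regression, at a modest cost in efficiency and in protection against chance imbalance

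*Protocol article*

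**What the plan says.** In the protocol article, Statistical analysis, the deciding test is fixed without covariates: "Primary and secondary outcome analyses including dichotomous data will be analyzed using Chi-squared test", with Fisher's exact test if numbers are small. A separate sentence then adds: "In addition a regression analysis depending on gender, lesion level, re-inclusion and indwelling urethral catheterization carriers". It ends by leaving both the list and the commitment open: "first-ever catheter or another significant or clinical relevant outcome will be considered".

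The baseline section (Socio-demographic and baseline clinical data) shows that the factors are recorded. It lists "date of birth, gender, level of spinal cord injury, traumatic or medical causes of spinal cord injury" and also "time with indwelling urethral catheter or first-ever urethral catheterization, presence of diabetes mellitus and medical treatments history (including treatments that may increase risk of infection".

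The Participants section, below Table 1, says that the population is mixed by design: "inclusion of patients with first-ever urethral catheterization and also patients with indwelling urethral catheterization as a method of voiding".

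Under Randomization, the only stratification factor is centre: "Blocked stratification for study centre is used to ensure that the two groups do not differ between centres".

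**The concern.** Patients with a first-ever catheter and established carriers may differ in infection risk, and so may patients who differ in sex, lesion level or diabetes. The design stratifies on none of these factors, and the primary test uses none of them. If they predict infection, a prespecified adjusted comparison would have more power with the same patients. It would also remove the part of any chance imbalance that they explain.

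As planned, the crude test decides even if the arms happen to differ in their share of carriers. The adjusted result would come from an optional regression with an open covariate list, so it would carry little weight beside the crude one. The planned power leaves almost no reserve, so even a small free gain is worth having.

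**Working it through.** **Inputs from the Statistical analysis section.** Control risk 24%; relative reduction 35%, so the silver-alloy risk is 0.24 × 0.65 = 15.6% and the difference is 8.4 points; two-sided alpha 0.05; 80% power; 371 per arm, 742 in total, allowing for 5% attrition.

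**Input not in the documents.** The share of outcome variance that the baseline factors explain (R²). Assumed range: 0.02 to 0.10, with higher values shown for context.

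**Step 1: the plan's own figure.** Two proportions, pooled variance under the null, no continuity correction, mean risk 0.198:
- n per arm = [1.960 × √(2 × 0.198 × 0.802) + 0.842 × √(0.24 × 0.76 + 0.156 × 0.844)]² / 0.084² = 353 after rounding up.
- 353 × 1.05 = 370.7, so 371 per arm and 742 in total: an exact match. Dividing by 0.95 instead gives 372 per arm and 744 in total.
- With 5% loss, 371 × 0.95 ≈ 352 per arm are evaluable, and power is 80.0%.

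The sample size is therefore right for the unadjusted test.

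**Step 2: power with adjustment (approximation).** Adjustment acts like an effective sample size of n / (1 − R²). The equivalent total is 742 × (1 − R²).

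| Assumed R² | Effective n per arm | Power | Equivalent total |
|---|---|---|---|
| 0 | 352 | 80.0% | 742 |
| 0.02 | 359 | 80.8% | 727 |
| 0.05 | 371 | 82.0% | 705 |
| 0.10 | 391 | 84.0% | 668 |
| 0.15 | 414 | 86.0% | 631 |
| 0.20 | 440 | 88.0% | 594 |

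**Step 3: check by simulation.** 3000 trials per scenario, 352 per arm, marginal risks held at 24% and 15.6%, four binary covariates with assumed prevalences of 20% to 50%, without centre.

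| Odds ratio of each covariate (assumed) | R² | Chi-squared | Adjusted logistic | Gain in points |
|---|---|---|---|---|
| 1.5 | 0.03 | 80.6% | 81.3% | 0.7 |
| 2.0 | 0.07 | 79.7% | 82.7% | 2.9 |
| 2.5 | 0.12 | 80.6% | 84.4% | 3.8 |
| 3.0 | 0.16 | 79.3% | 85.7% | 6.5 |

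Gains are taken from unrounded powers. With no treatment effect, both tests rejected in 4.4% to 5.7% of trials, so both keep their level.

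**Step 4: chance imbalance.** Suppose half the patients are carriers, with 32% risk in carriers and 16% in first-ever patients (assumed).
- SD of the between-arm difference in carrier share = √(2 × 0.25 / 352) = 3.8 points, so two SDs are 7.5 points.
- Shift in the crude risk difference = 7.5 × 0.16 = 1.2 points, against the planned 8.4.
- Standard error of the risk difference = √[(0.24 × 0.76 + 0.156 × 0.844) / 352] = 3.0 points, so the shift is about 0.4 standard errors.
- This assumed doubling of risk corresponds to R² = 0.25 × 0.16² / (0.24 × 0.76) = 0.035. An R² of 0.10 would need clearly stronger prediction than this one factor.

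**The case against.** The case for leaving the plan alone is substantial. A prespecified unadjusted chi-squared test is a valid analysis of a 1:1 randomised binary outcome, and the sample size was computed for it. Randomisation balances the factors in expectation, and the 5% level already allows for chance imbalance. A crude primary test with adjusted support is a conventional order. The gain rests entirely on assumed prognostic strength. The Discussion also describes urinary symptoms in this population as poor in sensitivity and specificity, and noise of that kind in the outcome tends to weaken covariate associations. All of this stands, and it limits the point to an improvement.

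Two stronger readings are tempting and are not supported. A reader might infer that the primary test is biased or underpowered; Steps 1 and 3 show that it is neither. A reader might also infer that the protocol itself calls these factors risk factors for infection. It lists gender, lesion level and catheter history only as regression terms. It attaches raised infection risk only to certain treatments in the medical history. Diabetes appears in the baseline list but not among the named regression terms.

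It could be said that model details belong in an analysis plan that is not shown. That does not dispose of the point: the article itself makes the unadjusted test primary and the regression additional and optional, and it is this stated choice that is questioned.

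**Conclusion.** The point holds as a low-cost improvement, not as the correction of an error. The primary test leaves unused baseline information that the trial collects and in large part already names for a regression. The likely cost is about 1 to 4 points of power at R² of 0.02 to 0.10, roughly 15 to 74 of the 742 patients (742 × 0.02 and 742 × 0.10). If the factors predict weakly, almost nothing is lost. A two-SD imbalance in carrier share would move the estimate by about 1.2 points under the assumed doubling of risk, which is noticeable but well within sampling error.

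These sizes rest on the assumed R², prevalences and risks, on 352 evaluable patients per arm, and on treating all randomised entries as independent. The article allows the same patient to be randomised more than once; that is a separate matter and is not used here.

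**What to change.** Rewrite the primary analysis as a logistic model with arm, centre (the stratification factor) and a fixed list of pre-randomisation covariates: carrier versus first-ever catheter, gender, lesion level and diabetes. Report the effect as a standardised risk difference and risk ratio with 95% confidence intervals, which keeps the scale of the planned 8.4-point difference. Remove the open-ended term from this model; it speaks of an outcome where a baseline covariate appears to be meant. Keep the unadjusted chi-squared test as a supporting analysis.

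Fix the grouping of lesion level, and a rule for pooling small centres, before any outcome data are seen. Under the planning assumptions about 352 × 0.24 + 352 × 0.156 ≈ 139 events are expected. With ten recruiting centres (nine terms), arm and four single-term covariates, the model has 14 terms, or about 10 events per term. That is workable, but it leaves no room for a long list.

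The cost is wording only. No extra patients or data are needed, since centre and all four covariates are already recorded, and the sample size can stay at 742.
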